**Exclusion criteria**
• Prior diagnosis of type 1 or 2 diabetes mellitus, chronic or acute renal insufficiency, coronary disease clinically evident (acute myocardial infarction, chest angina, myocardial revascularization) or cardiac insufficiency, or history of prior cardiovascular events (AMI, CVD, or CABG).
• Significant chronic disease (terminal stage cirrhosis or hepatic disease or cancer) that affects the survival of patients at 24 months.
• Chronic inflammatory diseases except obesity (lupus, rheumatoid arthritis, etc.).
• Blood arterial pressure >140/90.
• Acute infection of any etiology within 4 weeks prior to the beginning of the study.
• Use of steroid hormones or NSAIDs 4 weeks prior to the beginning of the study.
• Patient enrolled in a program or treatment to lose weight, 8 weeks prior to the study entry.
• Patient requiring treatment with immunosuppressive agents, for any circumstance.
• Patient who has participated in a clinical trial in the 8 weeks prior to the study entry.
• Patient who requires a major surgical procedure during the next 12 months, after enrollment (Abdominal or thoracic surgery, vascular, neurosurgery, urologic or gynecologic surgical procedure).
• Patient with history of severe chronic gastritis or any condition of the gastrointestinal tract that may affect the absorption and/or distribution of any drug administered orally.
• Alteration of the hepatic function tests.
• Triglycerides ≥ 600 mg%.
• Serum creatinin ≥ 1.5 mg/dl or calculated creatinin clearance (Cockroft's method) less than 50 ml/min.
• History of use of psychoactive drugs or abuse of alcohol.
• Positive pregnancy test in the screening visit.
• Concomitant treatment with any other antihypertensive drug.
• Contraindication to receive treatment with Candesartan.
• Pathological alterations of aortic or mitral cardiac valves (stenosis o insufficiency) or hypertrophy cardiomyopathy.
• Denial to sign informed consent, or any mental condition that makes the patient part of a susceptible population

#### Sample size

A sample size of 84 subjects was estimated, considering a crossover clinical trial design as proposed by Hills and Armitage [70], accepting a type I error of 0.05, a power of 90%, and assuming a difference of 20 % in the HOMA index after 6 months of treatment with Candesartan (3 to 2.4) and a maximum standard deviation of 1.5. The final size of the sample, adjusted for a drop-out of 8%, is 100 subjects (50 in each group). The sample size ensures a power of 90% to detect differences in fasting glycemia of at least 8 mg/dL (0.44 mMol/L) with a standard deviation (SD) of 20 mg/dL (1.1 mMol/L), or a difference of 14 mg/dL (0.77 mMol/L) in the 2 hours post load glycemia with a SD of 40 mg/dl (2.2 mMol/L).

### Procedures

#### Enrollment

This study will be realized in an adult population with a maximum enrollment period of one year. Screening visit will include a semi-structured interview, anthropometry and blood pressure evaluation. Eligible subjects will be scheduled one week later for "Visit A", to perform a new interview, a physical examination and to withdraw blood samples, after a 10 hour fasting period, to determine plasma glucose levels, lipid profile, hepatic and kidney function and OGTT. Those who fulfill screening criteria will be included in a run-in phase to receive placebo and the standard treatment with TLC. The patients will be blinded during this phase, which will last 2 weeks. The patients with a compliance equal or greater than 80% during this "Run in" phase will be included in the study.

### Baseline assessments

Visit B will include measurements of blood pressure, anthropometric parameters, OGTT and electrocardiogram. A fasting blood sample and a 24 hour urine sample will be taken and stored (-70°C) to determine glucose, HbA1c, insulin, IL-6, leptin, resistin, adiponectin, tisular plasminogen activator (tPA), PAI-1, oxidized/reduced glutathione, malonaldehyde and 8-isoprostanes in urine. Once the patient completes the foregoing steps, during visit 1 he/she will be randomized to one of the arms of the treatment. For this purpose, a randomization system by blocks of 4 will be used. New tests will be performed at the end of each treatment, according to the study flowchart (Table 2). Randomization and preparation of medication/placebo will be done by AstraZeneca at Mölndal, Sweden.

**Table 2 T2:** Study flowchart.

**Visit**	**Screening**	**A**	**B**	**1**	**2**	**3**	**4**	**5**	**6**	**7**	**1a**	**2a**	**3a**	**4a**	**5a**	**6a**	**7a**	**8a**	
**Week**	**-4**	**-3**	**-1**	**0**	**1**	**4**	**8**	**12**	**16**	**20**	**24**	**25**	**28**	**32**	**36**	**40**	**44**	**48**	**52**
**Passive Follow up**																			x
**Nurse interview**	x	x	x	x	x	x	x	x	x	x	x	x	x	x	x	x	x	x	
**MD interview**		x	x	x	x	x		x			x	x	x		x			x	
**Medication delivery**		x		x		x	x	x	x	x	x		x	x	x	x	x		
**Physical examination**	x			x	x	x		x			x	x	x		x			x	
**Randomization**				x															

**Sample withdrawing**		x	x			x		x			x		x					x	
**Sample storage**			x								x							x	
**ECG**			x																
**Hemogram**			x								x							x	
**Plasma glycemia**						x		x					x		x				
**Lipid Profile**		x									x							x	
**Hepatic Function test**		x									x							x	
**Renal Function test**		x									x							x	

**OGTT**		x									x							x	
**Insulin**			x								x							x	
**CRP**				x							x							x	
**IL-6**				x							x							x	
**Hb A1c**				x							x							x	
**Leptin**				x							x							x	
**Resistin**				x							x							x	
**Adiponectin**				x							x							x	

**TPA**				x							x							x	
**PAI-1**				x							x							x	

**8-Isoprostanes**				x							x							x	
**Malonaldehyde**				x							x							x	
**Oxi/Red Glutathione**				x							x							x	

### Active follow-up

Seven days after beginning the treatment, and every month thereafter, the subjects will be asked to return for a visit in order to verify compliance, evolution of blood pressure and occurrence of adverse events. In the months 1 and 3 of each treatment, new fasting glucose determination will be done in all subjects. All basal measurements will be repeated at the end of each treatment (every 6 months).

### Passive follow-up

All the subjects will undergo a passive follow-up (telephonic follow-up) 30 days after concluding the treatment.

### Blood samples

In fasting conditions (at least 10 hours), blood samples will be taken from the antecubital vein, with appropriate conditions of asepsia and antisepsia, using 3 vacutainer tubes, one dry, another with citrate, and the other containing EDTA. After 10 minutes in vertical position, all samples will be centrifugated at 3000 rpm during 15 minutes to extract the serum or plasma. Part of the samples obtained during visits B, 5 and 9 will be stored in Ependorf vials at -70°C until the end of the study.

#### Anthropometrical measurements

All anthropometrical measurements will be taken first thing in the morning after urine elimination, with the subject using light clothing and no shoes.

**Weight**: will be measured with the patient standing and then registered after rounding it to the nearest 200 grams. The weight scale will be calibrated to 0 before each measurement.

**Height**: will be measured using a metric tape with the patient standing against the wall in Frankfort's position, and the value marked by a ruler placed horizontally on the head of the patient.

**Heart rate**: number of beats per minute will be measured in the radial artery.

**Blood pressure**: will be taken twice (with a difference of 5 minutes between the measurements) using a mercury sphygmomanometer in 2 occasions on the right arm, with the patient comfortably seated, after a 5 minute rest. Systolic blood pressure (SBP) will be determined by the first audible sound (Korotkoff phase 1). Diastolic blood pressure (DBP) will be registered when the sound disappears (Korotkoff phase 5). The patient should not have smoked 30 minutes prior to the blood pressure measurement. The pneumatic arm cuff must cover 2/3 of the upperarm's length; its inferior border must be 2–3 cm over the antecubital space; the cuff will be slowly deflated. The mean blood pressure (MBP), will be calculated using the following formula [SBP+(2*DBP)]/3

**Waist circumference**: will be measured in 2 occasions with the patient in a standing position, with the arms on the sides and using a measuring tape adhered to a dynamometer that exerts a force of 750 gr. The measuring tape will be placed horizontally in a middle point between the iliac crest and the anterior costal border. The difference between the two measurements should not be more than 0.5 cm.

**Hip circumference**: will be measured in 2 occasions with the patient in a standing position with the arms on the sides of the body, using a measuring tape adhered to a dynamometer that exerts a force of 750 gr. The hip circumference will be assessed over the major trochanters. The difference between the two measurements should not be more than 0.5 cm.

**Waist-Hip Relation (W/H-R): **will be obtained from the ratio between the waist and hip circumferences.

**Antero-posterior diameter**: will be measured twice with the patient in a decubitus supine position, using a ruler perpendicular to the bed and registering the cutting point with the tape applied horizontally on the abdomen. The difference between the two measurements should not be more than 0.5 cm.

**Body Mass Index (BMI)**: This index will be estimated using the weight in kilograms divided by the second power of the height expressed in meters.

#### Biochemical markers

Routine clinical test and inflammation markers will be processed in the Clinical Research Laboratory from the "Fundación Cardiovascular de Colombia" (Floridablanca, Colombia). The measurement of oxidative stress markers will be processed in the laboratories of Complutense University (Madrid, Spain).

**Glycemia, Lipid profile, Serum Creatinine, Hepatic enzymes (AST/ALT) **will be quantified by a routine colorimetric method. (Biosystems BTS-303 Photometric, España).

**Glycosylated Hemoglobin A1c: **Will be determined with a quantitative automated technique GlycoHemoglobin Analyzer (DCA 2000+ Bayer^®^.) using a whole blood sample.

**Insulin, High-sensitivity C-Reactive Protein and Interleukin 6: **will be determined by high sensitivity chemoluminescent inmunoassay technique (IMMULITE ^® ^Automated Analyzer, Diagnostic Products Corporation, Los Angeles, USA).

**Leukocyte count and differential formula: **will be determined by an automated counter (Baker System 9120 AX ^®^, Biochem Inmunosystem, USA).

**Glucose Tolerance Test: **will be done after a fasting period of at least 10 hours. After urine elimination, an intravenous catheter will be placed in the antecubital vein and blood samples will be withdrawn to assess the baseline blood glucose, then, a glucose load equivalent to 75 gr diluted in 300 mL of water will be administered to each study subject within a period of no more than 10 minutes. Then, after 2 hours, a new blood sample will be withdrawn to assess glycemia. Patients should not eat anything or do any exercise during the test.

**Serum Leptin, resistin and adiponectin: **will be measured by ELISA technique.

**HOMA Index**: Will be obtained from a mathematical model using the following formula:

HOMA=(Glycemia(mg/dL)18.02)∗Insulinemia(mU/mL)22.517
 MathType@MTEF@5@5@+=feaafiart1ev1aaatCvAUfKttLearuWrP9MDH5MBPbIqV92AaeXatLxBI9gBaebbnrfifHhDYfgasaacH8akY=wiFfYdH8Gipec8Eeeu0xXdbba9frFj0=OqFfea0dXdd9vqai=hGuQ8kuc9pgc9s8qqaq=dirpe0xb9q8qiLsFr0=vr0=vr0dc8meaabaqaciaacaGaaeqabaqabeGadaaakeaacqWGibascqWGpbWtcqWGnbqtcqWGbbqqcqGH9aqpdaWcaaqaamaabmGabaWaaSaaaeaacqWGhbWrcqWGSbaBcqWG5bqEcqWGJbWycqWGLbqzcqWGTbqBcqWGPbqAcqWGHbqycqGGOaakcqWGTbqBcqWGNbWzcqGGVaWlcqWGKbazcqWGmbatcqGGPaqkaeaacqaIXaqmcqaI4aaocqGGUaGlcqaIWaamcqaIYaGmaaaacaGLOaGaayzkaaGaey4fIOIaemysaKKaemOBa4Maem4CamNaemyDauNaemiBaWMaemyAaKMaemOBa4MaemyzauMaemyBa0MaemyAaKMaemyyaeMaeiikaGIaemyBa0MaemyvauLaei4la8IaemyBa0MaemitaWKaeiykaKcabaGaeGOmaiJaeGOmaiJaeiOla4IaeGynauJaeGymaeJaeG4naCdaaaaa@680B@

### Quality assurance systems

The inter- and intra-assay variation coefficient will be determined for all measurements. In order to eliminate the inter-assay error, all biochemical determinations will be performed at once.

### Data processing and quality assurance

All study data will be collected by trained personnel. These data will be recorded on forms previously designed for such purpose (Case Report Form-CRF). After completing the CRF, a monitor will review them to assure that they are correctly filled and legible. All corrections will be done by the monitor according to the Good Clinical Practice guidelines. Then, the information will be typed and stored twice in independent data base. A computer program (Epi-Info 2000) will be used to compare both database. Every discrepancy will be printed and corrected using the original CRF as reference.

### Data monitoring

The study coordinator will make sure that data is adequately collected. He/she will register the study visits and the time of data collection and the different procedures, as well as the compliance to the treatment.

### Data management

The FCV Research Institute will be responsible for the data management. Once the data is correctly recorded, the means and ranges will be estimated and the relevant variables will be crossed to identify inconsistencies or extreme values which could result from errors in data management (internal consistency analysis). Any detected error will be corrected using the original form and the lab reports as references, maintaining the 2 original database untouched.

Modifications and statistical procedures during the data analysis will be documented in the Stata 9.0 program, which will allow the replication of the data analysis whenever necessary.

### Statistical analysis

The study is set forth as an efficacy study of Candesartan in the improvement of the insulin sensibility and the OGTT results. The averages and proportions with their corresponding 95% confidence intervals will be obtained in a descriptive analysis for all clinically relevant variables measured during the baseline evaluation. In order to evaluate the presence of differences between the groups, the Student's paried *t- *test, the Wilcoxon's signed-rank test or the McNemar's test will be used according to the variable's characteristics. Linear multiple regression will be used with the purpose of comparing the results of the treatments. The analysis will be performed by the intention-to-treat approach. A p value under 0.05 will be considered as statistically significant.

The primary endpoint for the analysis will be the change in the value of HOMA index, fasting glucose and post-charge glucose plasma levels. The secondary endpoint for the analysis will include the changes in serum insulin, leptin, adiponectin, resistin, CRP, IL-6, tPA/PAI-1 ratio, Oxidized/Reduced glutathione ratio, malonaldehyde and 8-isoprostanes.

Treatment safety will be evaluated by the clinical history review and the statistics of the reported adverse events.

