#### Study treatments

▪ **Treatment A: **Candesartan 16 mg (one tablet per day) taken with breakfast during 4 weeks and then increased to the optimal dose of 32 mg/d (two tablets) during the next 20 weeks, depending on the subjects' tolerance.

▪ **Treatment B: **Placebo tablets administered similarly to treatment A, one tablet daily during 4 weeks and then 2 tablets per day during the next 20 weeks.

All the subjects will be included in a therapeutic life-style change program (TLC: educational, nutritional and exercise support) during the study.

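### The paired tests named for this two-period cross-over have no period term, and the regression is not tied to a period-adjusted form

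*Protocol article*

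**What the plan says.** The Study design and Study groups sections set out a randomised, placebo-controlled cross-over. One group takes candesartan for 24 weeks and then placebo for 24 weeks; the other takes them in reverse order. The Sample size section sizes the trial accordingly, "considering a crossover clinical trial design as proposed by Hills and Armitage". Under Study treatments, "All the subjects will be included in a therapeutic life-style change program", and this support lasts throughout the study.

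The Statistical analysis section then names the tests. It begins "In order to evaluate the presence of differences between the groups, the Student's paried" t test and adds the Wilcoxon signed-rank and McNemar tests, to be chosen by type of variable. It continues: "Linear multiple regression will be used with the purpose of comparing the results of the treatments". It also states: "The analysis will be performed by the intention-to-treat approach". The article names no period, sequence or subject term.

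**The concern.** In a two-period cross-over, each subject's difference (candesartan minus placebo) contains the treatment effect plus or minus any difference between the periods. The sign depends on the sequence. A one-sample test on the pooled differences leaves that shift in two places:

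- **In the error term.** The two sequences scatter around different means, so the estimated standard deviation is too large and power is lost.
- **In the estimate.** If the sequences finish with unequal numbers, the plus and minus shifts no longer cancel.

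A period effect is plausible here. Subjects already in a weight-loss programme are excluded (Table 1), so the lifestyle support is new to those enrolled, and it bears on HOMA and glucose, the primary endpoints.

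There is also a wording fault. The paired tests are said to assess differences between groups, but the Study groups section defines the groups as the two sequences, which are different people. A paired test compares treatments within subjects, not one sequence with the other.

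**Working it through.** **Inputs from the Sample size section.** HOMA effect 0.6 (3 to 2.4); SD 1.5; type I error 0.05 (taken as two-sided); power 90%; 84 subjects before drop-out and 100 after (50 per group). **Assumed, because the article gives no figure:** the period effect (0 to 0.9 HOMA units, the difference between periods common to both sequences) and the split of completers.

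**The plan's own figure.** Paired form: N = (SD × (1.960 + 1.282) / effect)² = (1.5 × 3.242 / 0.6)² = 65.7, so 66. The stated 84 follows only if 1.5 is the SD of a single measurement and the within-subject correlation is about 0.36. The SD of the difference is then 1.5 × √(2 × 0.64) = 1.70. The article does not say which is meant, so both 1.50 and 1.70 are used below.

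**Does period adjustment need more subjects?** Comparing period differences between sequences, the contrast is 2 × 0.6 = 1.2. Then n per sequence = 2 × (1.5 × 3.242 / 1.2)² = 32.8, so 33, or 66 in all. The total is unchanged.

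**Balanced completers (42/42), SD 1.50, period effect 0.6.**
- SD seen by the paired t test: √(1.5² + 0.6²) = 1.616.
- Standard error it uses: 1.616 / √84 = 0.176. True standard error: 1.5 / √84 = 0.164.
- Approximate power: Φ((0.6 − 1.96 × 0.176) / 0.164) = Φ(1.55) = 94%. Simulation gives 93.6%, against 95.3% adjusted.

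**Unequal completers.** Bias = period effect × (n1 − n2) / N.
- 46/38: 0.6 × 8 / 84 = 0.057, about 10% of the target effect.
- 50/34: 0.6 × 16 / 84 = 0.114, about 19%.

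**Simulation (20,000 trials per row, 84 completers, true effect 0.6 for power and 0 for type I error).**

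| SD of difference | Period effect | Split | Paired t: mean estimate | Paired t: power | Paired t: type I | Adjusted: power | Adjusted: type I |
|---|---|---|---|---|---|---|---|
| 1.50 | 0 | 42/42 | 0.60 | 95.4% | 4.8% | 95.4% | 4.8% |
| 1.50 | 0.6 | 42/42 | 0.60 | 93.6% | 3.6% | 95.3% | 5.1% |
| 1.50 | 0.9 | 42/42 | 0.60 | 90.8% | 2.2% | 95.2% | 5.1% |
| 1.50 | 0.6 | 46/38 | 0.66 | 96.6% | 4.5% | 94.9% | 4.8% |
| 1.50 | 0.6 | 50/34 | 0.72 | 98.6% | 8.2% | 94.7% | 5.1% |
| 1.50 | 0.9 | 50/34 | 0.77 | 99.1% | 10.9% | 94.6% | 4.8% |
| 1.70 | 0 | 42/42 | 0.60 | 89.2% | 5.1% | 89.2% | 5.1% |
| 1.70 | 0.6 | 42/42 | 0.60 | 87.0% | 3.7% | 89.4% | 5.0% |
| 1.70 | 0.9 | 42/42 | 0.60 | 83.6% | 2.7% | 89.4% | 5.0% |
| 1.70 | 0.6 | 46/38 | 0.66 | 92.3% | 4.5% | 88.9% | 4.8% |
| 1.70 | 0.6 | 50/34 | 0.72 | 95.8% | 7.4% | 88.2% | 5.0% |

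The adjusted estimate stays at 0.60 in every row. The higher paired-t power in the unequal rows comes from bias; if the other sequence lost more subjects, the bias would have the opposite sign.

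**How extreme are the splits?** Going from 100 to 84 loses 16 subjects. From 50/50, a 46/38 split means losses of 4 and 12; a 50/34 split means all 16 fall in one sequence.

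**The case against.** The strongest defence is that the paired tests are sound within-subject tests and the harm is small. Allocation is 1:1 in blocks of 4 (Baseline assessments). If completion is similar in both sequences, the paired t test is unbiased and errs on the conservative side. With an SD of the difference of 1.5, its power stays above 90% even at a period effect of 0.9. A period effect of 0.6 is as large as the whole assumed drug effect; at 0.3 the 46/38 bias is only 0.3 × 8 / 84 = 0.029. Even at 0.6, a 46/38 split does not raise the type I error above 5%. All this stands, and it limits the weight of the point.

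Three stronger readings are tempting but not supported:

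- **That the regression is ordinary and treats a subject's two results as independent.** The article gives neither its terms nor its unit of analysis. Regressing within-subject differences on sequence is itself linear regression and is period-adjusted. Such detail may sit in an analysis plan that is not shown, so no loss from an unpaired regression is established.
- **That the intention-to-treat analysis is really a completers' analysis.** A paired test needs both values, but the article does not say how a missing one is handled, and that is commonly left to the analysis plan.
- **That the tests depart from the basis of the sizing.** They keep the pairing, and the required number is the same with or without a period term.

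What the defence does not remove is that the article chose specific tests, and those tests have no period term. Blocked randomisation balances entry, not completion.

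**Conclusion.** The point holds in a limited form and deserves a clarification before analysis; it does not invalidate the trial. The named paired tests omit period in a design where a period trend is plausible. With equal completion the cost is power alone: about 2 points at a period effect of 0.6 and 4 to 6 points at 0.9. With unequal completion there is bias of about 0.06 (46/38) or 0.11 (50/34) at a period effect of 0.6. Type I error is 7-8% at the extreme 50/34 split.

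A reader might conclude that the paired tests always mix the lifestyle trend with the treatment effect. For the estimate, that is true only when the sequences complete unequally. These figures rest on 84 completers, an SD of the difference of 1.5 or 1.70, and assumed period effects and splits. They were worked for the t test. The signed-rank and McNemar tests lack a period term in the same way, though McNemar matters little because every listed primary and secondary endpoint is a continuous measure.

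**What to change.** State that the treatment comparison is period-adjusted and within subject, in one of two forms:

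- a linear mixed model with treatment, period and sequence as fixed effects and a subject effect, using every randomised subject with at least one end-of-period value, which also serves the stated intention-to-treat approach; or
- a two-sample comparison (t or rank-sum) of within-subject period differences between the two sequences.

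Say that the planned linear multiple regression takes this form. Reword the sentence on the paired tests so that it refers to differences between treatments within subjects, not between groups. Analysing HOMA on the log scale is optional and not part of this correction.

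The cost is a change of wording and about one degree of freedom. No extra subjects, visits or measurements are needed.

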### Ethical aspects

The clinical trial will be conducted according to the Helsinki's Declaration, the Good Clinical Practice Guidelines and the Colombian legislation (Resolution 8430/93 of the Ministery of Health). The patient will provide written informed consent in a form designed for such purpose. The information generated by the study will be confidential and strictly limited to the purposes stipulated in the protocol. The patient may refuse to continue participating in the study at any moment after providing his/her consent. The study has been approved by FVC ethics committee. All assessments will be performed by trained staff. The blood samples will be collected in aseptic conditions by an expert bacteriologist.

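### Intention-to-treat is promised, but the paired tests named leave out any subject without both a week-24 and a week-48 value, and the regression named does not clearly bring them back

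*Protocol article*

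**What the plan says.** The Statistical analysis section fixes the principle: "The analysis will be performed by the intention-to-treat approach". For differences between the groups it names Student's paired t-test and continues: "the Wilcoxon's signed-rank test or the McNemar's test will be used according to the variable's characteristics". The next sentence adds a second method: "Linear multiple regression will be used with the purpose of comparing the results of the treatments". The primary endpoint has three parts: "The primary endpoint for the analysis will be the change in the value of HOMA index, fasting glucose and post-charge glucose plasma levels".

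On timing, Active follow-up says: "All basal measurements will be repeated at the end of each treatment (every 6 months"). Table 2 marks insulin and the OGTT after randomisation at weeks 24 and 48 only. Fasting glucose has extra values at months 1 and 3 of each treatment (weeks 4, 12, 28 and 36).

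On losses, Sample size says: "The final size of the sample, adjusted for a drop-out of 8%, is 100 subjects (50 in each group"), starting from 84. Ethical aspects says: "The patient may refuse to continue participating in the study at any moment after providing his/her consent".

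**The concern.** Intention-to-treat means that all randomised subjects are compared as assigned. A paired test can use only subjects with both members of the pair. For HOMA and the 2-hour glucose there is one measurement per period, so one missed visit removes the subject from the comparison, including the value already obtained. If the paired result is reported as intention-to-treat, readers will take it as applying to everyone randomised.

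This matters if loss is related to treatment. The Study treatments section makes the dose step depend on tolerance, so tolerability problems are foreseen. In a crossover, loss in either period breaks the pair, so the comparison is exposed to two periods of attrition.

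**Working it through.** **1. What each named method does with a subject who has only one of the two values**

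- Paired t, signed-rank, McNemar: no pair, so the subject is left out.
- Linear regression on within-subject differences: no difference, so left out.
- Linear regression with subject as a fixed effect: the single value is absorbed by the subject's own intercept and adds nothing to the treatment contrast.
- Linear regression pooling both periods without a subject term: the subject is kept, but the two correlated values of everyone else are treated as independent, so the standard error is wrong.
- Linear regression on period 1 alone: subjects lost later are kept, but the crossover comparison on which the sample size rests is given up.

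The article does not say which regression is meant. None of these forms both keeps one-period subjects and respects the crossover.

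**2. The plan's own drop-out figure**

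Inputs from Sample size: 84 before drop-out, 8% drop-out, 100 final.

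- 8% overall: 84 / (1 − 0.08) = 91.3, so 92. This does not give 100.
- 8% in each period: 84 / 0.92² = 99.2, so 100. This reproduces the figure, but the text does not state it.

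**3. Subjects outside the paired comparison, out of 100 randomised**

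- 8% overall: 100 × 0.92 = 92 pairs, 8 left out.
- 8% per period: 100 × 0.92² = 84.6 pairs, about 15 left out.

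**4. How many a model that keeps one-period subjects would recover**

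With 8% per period, 100 × 0.08 = 8 are lost before week 24 and 92 × 0.08 = 7.4 between weeks 24 and 48. The mixed model recovers the 7.4. The first 8 have no HOMA value after randomisation and are recovered only if they are still measured. With 8% overall, the number recovered lies between 0 and 8, depending on when the losses fall. Both parts of the fix are therefore needed.

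**5. Power if everyone is kept (illustration)**

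Assume two-sided 0.05, all 100 measured in both periods, and no effect in the 8 to 15 who would otherwise be missing. The planned HOMA difference of 3 − 2.4 = 0.60 becomes 0.60 × 0.92 = 0.552 or 0.60 × 0.8464 = 0.508. Power = Φ(difference × √100 / SD − 1.96).

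- SD of the difference 1.5: Φ(3.68 − 1.96) = 95.7% and Φ(3.39 − 1.96) = 92.3%.
- SD of the difference 1.70: 90.2% and 84.9%.

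Both SDs are shown because the article does not say what its 1.5 refers to. As the SD of the difference it gives (1.5 × 3.2415 / 0.6)² = 65.7, so 66 subjects rather than 84; an SD of the difference of about 1.70 gives 84. That mismatch is a separate matter and does not affect this point.

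**The case against.** The strongest reply has four parts.

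- **Pairs are not the only method.** A reader might infer that treatments are tested only in pairs. That is wrong: multiple linear regression is the method expressly assigned to comparing treatments. What stands is that its form is open, and the forms covered by that name do not resolve the conflict.
- **Stopping tablets is not leaving the study.** A reader might infer that anyone who stops early is lost. No section says so. Ethical aspects gives only the usual right to leave, and a subject off tablets who attends weeks 24 and 48 forms a complete pair and is analysed as assigned. A dose step that depends on tolerance also means that poor tolerance need not lead to stopping. This reply stands: the loss concerns missing visits.
- **Timing.** A reader might infer that an early stopper's endpoint could be taken on the day of stopping. Treatments are defined as 24 weeks, Baseline assessments refers the tests to the flowchart, and Table 2 fixes weeks 24 and 48. Scheduled visits are the natural reading, and one sentence would settle it.
- **Detail left elsewhere.** Missing-data rules and analysis-set definitions commonly sit in the full protocol or SAP, so their absence here is no finding. The point does not rest on that absence. It rests on two things the article does state, the intention-to-treat label and the paired tests.

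**Conclusion.** The point holds in this limited form. For HOMA and the 2-hour glucose, the named paired tests compare only subjects measured in both periods, and the regression as named does not repair this. Fasting glucose is less exposed because it also has values at months 1 and 3 of each treatment. The part left out is 8% of those randomised if the stated drop-out is overall, and about 15% if it applies to each period; the second figure is an inference from the step from 84 to 100. Both assume that drop-out means a missing week-24 or week-48 value.

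A reader might infer that the reported effect would be about 9% to 18% too large (0.60 / 0.552 = 1.09; 0.60 / 0.508 = 1.18). The document does not support this. The figure only restates the assumption of no effect in those lost, and it takes 0.60 to be a completer effect, which Sample size does not say. The direction and size of any bias are unknown.

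**What to change.** In Statistical analysis:

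- Make the treatment comparison a linear mixed model with treatment and period as fixed effects and subject as a random effect.
- Include every randomised subject with at least one post-randomisation outcome, analysed by assigned treatment in each period.
- Call this a modified intention-to-treat set, because subjects with no outcome after randomisation are still absent.
- Label any paired test a both-periods completer analysis.

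In Active follow-up, state that the week-24 and week-48 measurements are taken in all randomised subjects who have not withdrawn from the study, whether or not tablets are still taken.

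The cost is wording, since the visits and tests are already scheduled, plus some effort to follow subjects who are off tablets. The effect may be diluted, with power as in step 5. The model also relies on missing values being explained by the data observed, which should be stated.
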